#### Target detection index

**Intersection over union (IOU):**

$A_{a}$
 represents the predicted bounding box, 
$A_{m}$
 represents the true bounding box. IOU is shown in equation:

$$\begin{array}{c} IOU=\frac{A_{a}\cap A_{m}}{A_{a}\cup A_{m}} \end{array}$$

#### Segmentation index

**Dice:** Pred is the predicted tumor area, and true is the real tumor area. Dice is shown in equation (Milletari et al., 2016):

$$Dice=\frac{2*\left(pred\cap true\right)}{pred\cup true}$$

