**Methods:**

This is a double-center, ambispective, diagnostical observational study. One public database named the 2019 Brain Tumor Segmentation challenge dataset (BraTS) and two original datasets, including the Second Affiliated Hospital of Nanchang University, and Renmin Hospital of Wuhan University, will be used to develop the multi-task DL radiomic model. As one of the LB techniques, circulating tumor cell (CTC) parameters will be additionally applied in the DL radiomic model for assisting the “integrated diagnosis” of glioma. The segmentation model will be evaluated with the Dice index, and the performance of the DL model for WHO grading and all molecular subtype will be evaluated with the indicators of accuracy, precision, and recall.

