### Model development preprocess

Each patient in the dataset had MR scans of four sequences: T1C, T1, T2, T2 flair, and tumor mask, along with classification labels.

The goal of this network is to segment three regions of glioma, including enhanced tumor area (ET), non-enhanced tumor area (NET), and edema area (ED); The tumor’s location, size, and classification information obtained from the target detection network were combined with the CTC numerical feature to differentiate the histological type and molecular type.

Four different experienced neurosurgeons, who also received guidance from a senior neuroradiologist (>10 years of clinical experience), applied Segmentation and Segment Editor modules to manually segment the original MRI dataset. All scans have been co-registered to the same anatomical reference using a rigid transform method on the 3D-slicer registration module. Skulls of the brain MRI were removed by 3D-slicer software that can eliminate the influence of skull areas with high-intensity signals. MR scans often display intensity non-uniformities due to variations in the magnetic field. Therefore, N4 bias field correction was used before the image input. We use data augmentation to increase the size of the dataset. To prevent over-fitting in training, data augmentation was used to expand the dataset.

The data augmentation methods used are as follows: (1) Adding random noise to the voxel, the noise worth ranged between −0.1 times and 0.1 times the standard deviation of the voxel. (2) Image size was changed to the original 0.9–0.1 times. (3) Random rotation and translation, with rotation ranging from −20 to +20°, and translation ranging from −30 to +30 and −15 to +15, respectively. (4) Random flip.

According to the 2021 WHO classification criteria, the molecular types of glioma were divided into 11 subcategories, and the histological type was divided into three grades. The grades, segmentations, and subcategories labels of each patient were one-hot encoded. In the preprocessing step, anchor boxes of the tumors were automatically generated according to the segmentation labels. The anchor box was the ground truth of the target detection task.

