### Segmentation part

The segmentation network was formed by extending the upsampled part of object detection until the obtained feature map has the same size as the input feature. The overall network structure was U-shaped, and the segmentation head divided the tumor into four regions: ET, NET, ED, and background.

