#### Segmentation loss

$$\begin{array}{c} L_{seg}=-\lambda_{seg}\sum_{c=1}^{C_{seg}}\log\frac{\exp\left(x\right)}{\sum_{C_{seg}}^{i=1}\exp\left(x\right)}y \end{array}$$

x
is the output of the segmentation head, 
y
 is the one-hot code of the segmentation label, 
$C_{seg}$
 represents the number of classes that need to be segmented, and 
$\lambda_{seg}$
 represents the segmentation loss.

The total loss function is the sum of the four loss functions, as shown in equation

$$\begin{array}{c} L_{\mathrm{object}}=L_{\mathrm{coord}}+L_{\mathrm{conf}}+L_{\mathrm{cls}}+L_{\mathrm{seg}} \end{array}$$

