**Figure 7 fig7:**
[figure not shown]
The cases of tumor area detection and segmentation via the proposed model. The three rows from top to bottom are the three views of three glioma samples, respectively. The left side is the prediction box obtained from the object detection part (green line) and the true mask of glioma segmentation (white), and the right side is the segmentation result predicted by the segmentation module.

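### The segmentation goal is three separate regions, but Dice, the only segmentation index, is worded on one undivided tumour area and so, read as written, cannot assess that goal

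*Protocol article*

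**What the plan says.** The section Model development preprocess states the task as a separation into parts: "The goal of this network is to segment three regions of glioma, including enhanced tumor area (ET), non-enhanced tumor area (NET), and edema area (ED"). Matching output classes are given in the section Segmentation part: "the segmentation head divided the tumor into four regions: ET, NET, ED, and background". The Segmentation loss is likewise summed over classes, with a symbol that "represents the number of classes that need to be segmented".

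On evaluation, the abstract's Methods paragraph says: "The segmentation model will be evaluated with the Dice index". The Segmentation index section names no other measure. It defines the two sets that enter Dice in one sentence, "Pred is the predicted tumor area, and true is the real tumor area", and prints a formula with twice the intersection over the union. It gives no region subscript, no statement that the formula is applied class by class, and no averaging rule.

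**The concern.** The task and the training loss distinguish three tumour regions; the index, as worded, distinguishes tumour from everything else. Once ET, NET and ED voxels all count as tumour, calling one region by another's name costs nothing. A network that only traces the outer edge of the lesion would be reported as equal to one that also separates the three regions, and the reported figure could not show whether the stated goal was met. If the choice between pooled and per-region Dice stays open, it can also be settled after both sets of values have been seen.

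**Working it through.** The article gives no Dice value, so there is no figure to reproduce. The check has two parts.

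**1. Which reading does the wording favour?**

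- Model development preprocess calls ET and NET tumour areas but ED an edema area. If tumour area in the Dice sentence were a generic region name, it would not fit one of the three targets.
- The section on the learning curve uses tumour area for the lesion as a whole.
- The Figure 2 caption gives the segmentation part a single tumour region to segment.
- The Figure 7 caption describes one mask: "the true mask of glioma segmentation (white").
- The Classification loss and Segmentation loss sections write a class index where a per-class quantity is meant. The Segmentation index section does not.

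The pooled reading is the more natural one, but no section states it outright.

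**2. What would pooled Dice miss?**

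Standard Dice = 2 × overlap / (predicted + true). Assumed lesion, not from the article: ET 20, NET 15, ED 65 mL, with the outer boundary found exactly.

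*Half of ET called NET* (predicted ET 10, NET 25, ED 65):
- ET: 2×10/(10+20) = 0.67
- NET: 2×15/(25+15) = 0.75
- ED: 2×65/(65+65) = 1.00
- Pooled: 2×100/(100+100) = 1.00

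*Every tumour voxel called ED* (predicted ET 0, NET 0, ED 100):
- ET: 0.00
- NET: 0.00
- ED: 2×65/(100+65) = 130/165 = 0.79
- Pooled: 1.00

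Sensitivity to the assumed split, using 10,000 tumour voxels all called ED with an exact boundary:

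| ET / NET / ED voxels | Pooled Dice | ED Dice | Mean of three regions |
|---|---|---|---|
| 2000 / 2000 / 6000 | 1.00 | 12000/16000 = 0.75 | 0.25 |
| 3333 / 3333 / 3334 | 1.00 | 6668/13334 = 0.50 | 0.17 |
| 500 / 500 / 9000 | 1.00 | 18000/19000 = 0.95 | 0.32 |

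ET and NET Dice are 0 in every row. If the three labels are rotated instead, so that no voxel keeps its own label, all three region values are 0 and pooled Dice is still 1.00.

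**Printed denominator.** With the union below the line, the pooled value is 2×100/100 = 2.00 in both 100 mL cases, and a perfect model also scores 2.00. The formula as printed equals twice the intersection over union and runs from 0 to 2. The scale changes, but the failure to tell these models apart does not.

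**Limit.** If the whole image is called ED (assumed 100,000 voxels, of which 10,000 are tumour), pooled Dice is 2×10000/(100000+10000) = 0.18, or 20000/100000 = 0.20 with the printed denominator. The top score therefore needs an exact outer boundary.

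**The case against.** The strongest reply is that the Dice sentence is a textbook two-set formula meant to be applied to each class. The neighbouring Classification index section is written the same way: accuracy, precision and recall use plain true and false positives and negatives with no class index, although the model has three grades and 11 molecular subcategories. The region names for ET and NET themselves contain the words tumour area, and the multi-class head and loss suggest multi-class scoring. A condensed article may also leave the reporting detail to a fuller document.

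Much of this stands. A reader might infer that the investigators have decided to pool the regions; the article does not say so. A reader might also infer that labelling everything as edema earns a perfect score; that holds only for tumour voxels inside a correct boundary, as the 0.18 shows. The volumes used above show what pooling would do, not what it will do in this study.

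The reply does not remove the point. The article did not leave the index to another document: it defined Dice and named its two inputs, and those inputs do not match the three-region task.

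It is also fair to say that the consequences are contained. The primary outcome is molecular type and the secondary outcome is WHO grade. The Classification part takes the box location, size and class features plus CTC features; ET, NET and ED labels are not listed among its inputs.

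**Conclusion.** The point holds as a mismatch between goal and index. As worded, the only segmentation index scores the whole-tumour outline and cannot show whether ET, NET and ED are separated. In the assumed examples, pooled Dice stays at 1.00 (2.00 as printed), while region values fall to 0.67, 0.75 and 1.00 when half of ET is called NET, and to 0, 0 and 0.50 to 0.95 when every tumour voxel is called ED.

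This rests on the pooled reading, which the wording favours but does not make certain, and on an exact outer boundary. The sizes depend on assumed region volumes. Whether pooled Dice conceals region confusion does not depend on those volumes.

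The importance is modest: segmentation is neither the primary nor the secondary outcome, and nothing here shows that the stated outcomes would be biased.

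**What to change.** In the Segmentation index section, define Dice for each region r in {ET, NET, ED}: the predicted set is the voxels predicted as r, the true set is the voxels manually labelled r, and the denominator is the sum of the two set sizes instead of their union. Report the three values. If an average is given, take it over the three regions without background. Whole-tumour Dice may stay as an additional line, named as such, but not as the evaluation of the three-region task.

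The cost is a short change to one definition. No new data are needed, since training with a multi-class loss already requires region labels, and the segmentation head outputs the regions. The downside is three values in place of one, which will usually be less favourable than the whole-tumour figure. If per-region Dice was intended all along, the same change simply says so.

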### Learning curve during the process of model training

We demonstrated the learning curves that show the training loss during the process of model training. First, the backbone, target detection, and segmentation parts are trained with the cosine annealing learning rate decay strategy. The loss value decreases steadily with the increase of the learning rate decay period. Figures 6A,B of the revised manuscript show the learning rate and loss function value curves in this stage. Then, the classification part was trained, which adopted the learning rate decay strategy of first warming up in 10 epochs and then declining in 150 epochs. The learning rate and three classification loss value curves are shown in Figures 6C,D. Figure 7 illustrates the cases of tumor area detection and segmentation via the proposed model in this study.

**Figure 6 fig6:**
[figure not shown]
Learning curves during the model training: **(A,B)** show the learning rate and loss function value curves in this stage; **(C,D)** show the learning rate and three classification loss value curves.

**Figure 7 fig7:**
[figure not shown]
The cases of tumor area detection and segmentation via the proposed model. The three rows from top to bottom are the three views of three glioma samples, respectively. The left side is the prediction box obtained from the object detection part (green line) and the true mask of glioma segmentation (white), and the right side is the segmentation result predicted by the segmentation module.

## Discussion

Preoperative and non-invasive diagnosis of the molecular subtype is very critical for glioma treatment. The combined methods of radiomics and LB have great potential to non-invasively diagnose glioma grading and molecular markers since they are both easy to perform. This is the first study that combing these two technologies for glioma diagnosis.

In this study, we apply multimodal MRI to construct a multi-task DL model, which the backbone of its network architecture is built by CSPNet. CSPNet solves the problem of large computation in inference from the perspective of network structure design (Wang et al., 2020). The authors of CSPNet argue that the problem of excessive inference computation is due to the duplication of gradient information in network optimization. Therefore, CSP is used to first divide the feature map of the basic layer into two parts, and then merge them through the cross-stage hierarchy, which can reduce the calculation amount while ensuring accuracy. In this protocol, a relatively lightweight DarkNet-tiny will be selected as the basis to fuse the CSP connection to form the final CSPDarkNet-tiny structure. In terms of algorithms, they are different from previous studies because most of them are built based on CNN purely (Shaver et al., 2019; Matsui et al., 2020; Choi et al., 2021; van der Voort et al., 2022).

To date, with the in-depth study of LB, CTC as an important branch has been applied to the non-invasive diagnosis of glioma. In our previous study (Qi et al., 2021), it has been confirmed that peripheral blood CTC is related to IDH mutant. However, the relationship between CTC and other important molecular targets has not been further explored, and we have not found other similar studies. In this study, we combine CTC count as a very important parameter with the DL model to explore its value in molecular and graded noninvasive diagnosis of glioma, which is unprecedented in the current study. However, it must be clarified that some glioma subtypes are assigned to fewer training samples and cannot rely on the model for subtype diagnosis. Therefore, we further proposed CTC sequencing of individual molecular targets as the basis for the diagnosis of glioma subtypes. Since the inherent black-box nature of deep learning models and less transparency, we will add relative modules to improve the understandability of existing models based on the premise of the stable prediction performance of the models in the future (Dasanayaka et al., 2022).

Since the publication of the WHO-CNS classification guidelines in 2021, scholars around the world have been committed to the application of radiomics or LB techniques to achieve “precisely integrated prediction” of gliomas before surgery, since the noninvasive prediction of important molecular markers is essential to guide the treatment of patients who are inoperable or have tissue biopsy. Simply relying on radiomics features to find the correlation with the molecular pathological features of gliomas can no longer meet the need for an accurate diagnosis of gliomas. CTC features are a promising biomarker that may provide new directions in the exploration of “precision diagnosis” based on the radiomics. How to combine the preoperative radiomics features, CTC features or other LB markers of glioma patients is the direction that requires the joint efforts of global scholars in the future, At the same time, it is necessary to provide matched molecular marker information of glioma patients to ensure the feasibility of the study.

We firmly believe that this innovative work will surely lay a good foundation for the “precisely integrated prediction” of glioma and shed a new direction for future research.

## Ethics statement

This study is conducted in accordance with the Declaration of Helsinki and the Code of Ethics for Human Medicine and Health Research and has been approved by the Ethics Committees of The Second Affiliated Hospital of Nanchang University (IIT-D-2022-003), Renmin Hospital of Wuhan University (WDRM2021-K109), and registered at ClinicalTrails.gov on September 10, 2022, with Identifier NCT05536024. All recruited patients signed informed consent.

